### Design and setting

This clinical trial examines the implementation of a diagnostic and risk stratification pathway for NAFLD in people with T2D. Sequential participants will be recruited to the NAFLD-RRR pathway and followed for up to 10 years to monitor their health outcomes. The detection of patients with NAFLD ± advanced fibrosis and the surveillance for HCC among “high-risk” patients will be compared to patients receiving “usual care”.

Due to the high prevalence of NAFLD and advanced fibrosis in people with T2D, it is not appropriate to conduct a randomized study of screening and risk stratification versus no intervention. All people attending the community diabetes clinics will be offered participation in the study. Study outcomes will be compared to a cohort who received “usual care” at the community diabetes clinics in the 12-months prior to implementation of the NAFLD-RRR pathway. The medical records of “usual care” patients will be audited to determine the number of people with a recorded diagnosis of NAFLD, whether an assessment of liver disease severity was performed, and the number of people referred to a liver clinic.

The study will be conducted in 3 “Beacon” diabetes clinics in the Metro South hospital and health services district (HHS), where people who are referred by their GP for specialist management of T2D are offered specialised care in a primary care setting. The Beacon model for people with complex T2D is delivered through community-based general practices where GPs with a special interest (GPwSIs) and advanced training in diabetes work alongside an endocrinologist and diabetes nurse educator [28]. The model is an alternative to standard hospital outpatient review and is fully integrated, with primary care providers and specialists co-located to provide effective, cost-efficient and patient-centred care [29]. In this model the GPwSIs take their enhanced skills back to their routine practice, so they become a referral point and source of knowledge for colleagues, potentially reducing referrals to specialist clinics. Prior to developing and implementing the NAFLD-RRR pathway, diabetes clinic/community clinicians (*n* = 24) were invited to participate in focus group discussions to obtain information about preferences and strategies for learning, support and communication [30].

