No NAFLD: Participants with CAP score < 248 dB and LSM < 8 kPa will be classified as “no NAFLD”. A letter will be sent to the patient’s GP and diabetes specialist advising a repeat FibroScan or liver ultrasound in 3–5 years if appropriate, to screen for development of NAFLD. Participants will be informed of their FibroScan result at the NAFLD-RRR appointment and advised to follow up with their GP.

NAFLD with low risk of clinically significant fibrosis: Participants with CAP score ≥ 248 dB and low FibroScan score (LSM < 8.0 kPa) will be classified as ‘Low Risk’. A letter will be sent to the patient’s GP and diabetes specialist advising a repeat FibroScan in 2–3 years if appropriate, to assess for development of clinically significant fibrosis. If liver enzymes are abnormal, the letter to the participant’s GP will include guidance for further evaluation of abnormal liver enzymes.

High risk of clinically significant fibrosis: Participants with LSM ≥8.0 kPa will be classified as ‘High Risk’. The study clinician will advise the patient (and GP and diabetes specialist via letter) that Hepatology referral is recommended. A letter will be sent to the patient’s GP advising them to arrange a Hepatology Clinic referral. To assist GPs with this process, referral guidelines will be included with the patient’s letter and FibroScan result. If advanced fibrosis is confirmed in the secondary care hepatology clinic, the patient may be offered ongoing hepatology follow-up that may involve HCC and variceal surveillance programs.

For all patients with NAFLD, the letter to the GP and diabetes specialist will provide recommendations regarding management of NAFLD with ongoing assessment and management of cardiometabolic risk factors and lifestyle intervention with consideration of referral to a dietician, exercise physiologist and psychologist for assistance with weight management and increased physical activity. Patients diagnosed with NAFLD at the study clinic visit will receive a patient letter at the conclusion of the clinic visit. This letter advises patients to make an appointment to see their GP to further discuss the recommendations advised by the study team. The template letters are provided in Supplementary Figs. 1-4.

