#### Secondary outcomes

***Rate of referral of “high-risk” NAFLD to Hepatology***. This will be calculated based on the number of “high-risk” patients referred to Hepatology clinics.***Rate of referral of “low-risk” NAFLD to Hepatology.*** This will be calculated based on the number of participants who receive a diagnosis of NAFLD without clinically significant fibrosis (LSM < 8.0 kPa), and the number of these “low-risk” patients that are referred to Hepatology clinics.***Rate of surveillance for HCC among “high-risk” patients.*** This will be calculated based on the number of participants with cirrhosis who are referred for surveillance for HCC according to guidelines (with liver imaging, usually ultrasound, every 6 months).***Collection of evidence about the economic benefits of a NAFLD detection/risk stratification pathway in people with T2D.*** Costs associated with the new pathway will be collected by the research team using published costing methods. Modelling will permit estimation of an incremental cost per appropriate referral via the pathway versus usual care that can be considered in light of undesirable consequences, including those associated with delayed detection and referral. Diagnostic performance of the pathway in identifying cases of advanced fibrosis will be compared with usual care.***Longitudinal outcome data.*** Participant outcome data will be collected at 12 months, 5 years and 10 years post recruitment. Linkage to Hospital Admitted Patient Data, Emergency Department data, Cancer Registry, and Death Registration will be performed by the Queensland Health Data Linkage Team for all participants. Data items will include: 1) details about hospital admissions and emergency presentations: dates, primary/other diagnosis, procedures and use of hospital-based allied health services and hospital-based clinical costings; 2) cancer (any type): date of diagnosis, site, morphology, differentiation, basis of diagnosis; 3) date and cause of death.***Development of procedures and referral pathways to facilitate patient access to required services.*** The study clinician will develop resources for the service (GP template letters). Knowledge and attitudes of clinic/community clinicians will be surveyed post-implementation of the pathway (at 2 years).***Collection of usual care data.*** Usual care data will be collected retrospectively from the three study sites for the year prior to recruitment commencement. Eligibility and exclusion criteria of controls will be the same as the intervention group except for patient consent (we will seek a waiver of consent to collect available data from patient medical records). The data collected for this usual care group will include demographic information, anthropometric measurements (height, weight, BMI, waist circumference), relevant metabolic co-morbidities, diabetes medications, and whether there is a record of alcohol consumption, a diagnosis of NAFLD and management of NAFLD – including risk stratification, blood tests, simple fibrosis scores, radiological investigations and/or referral to liver clinics.

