#### Resource use and costs

Healthcare resource use information will be collected for each of the pathways (NAFLD-RRR pathway and usual care). We will collect healthcare resource use information from two sources with equivalent availability for each group: administrative data collections from participating health services and auditing of clinical case note files. This will include capturing resource use related to the diagnosis of NAFLD, assessment of fibrosis, procedures and tests. Healthcare resource use will be costed from the healthcare funder perspective using actual costs (when available), market rates or published pricing information (where relevant).

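### Usual-care Hepatology referrals are counted from records at the three Beacon sites, although the patient's own GP can refer, so they may be under-ascertained relative to the pathway period, with opposite effects on high-risk and low-risk referral

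*Protocol article*

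**What the plan says.** **Control source.** Under Secondary outcomes (collection of usual care data), the protocol article states: "Usual care data will be collected retrospectively from the three study sites for the year prior to recruitment commencement". Controls are not asked for consent: "we will seek a waiver of consent to collect available data from patient medical records". The items to be extracted include a record of "radiological investigations and/or referral to liver clinics". Design and setting says the audit will determine "whether an assessment of liver disease severity was performed, and the number of people referred to a liver clinic".

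**Who refers.** Design and setting describes the Beacon clinics as a place where "people who are referred by their GP for specialist management of T2D are offered specialised care in a primary care setting". The patient's GP is thus normally outside the clinic. For high-risk pathway participants, the Intervention section says: "A letter will be sent to the patient’s GP advising them to arrange a Hepatology Clinic referral".

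**What is compared.** The Data analysis section tests the proportion referred to Hepatology (Aim 3) before and after implementation with tests for categorical data. Hypothesis H3 has two limbs: more referral of high-risk NAFLD and less of low-risk NAFLD. Secondary outcomes lists a referral rate for each and names no data source for the pathway period.

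**A second source, for costs.** Resource use and costs plans two sources of equivalent availability in both groups: "administrative data collections from participating health services and auditing of clinical case note files". The section concerns resource use, and its list of items does not mention referral.

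**The concern.** A before-after comparison of referral is only as good as its ability to see referrals equally well in both periods. The control count depends on a referral having reached the diabetes site's file. The clinician whom the protocol treats as a referrer works elsewhere, and that GP's records are not named as a source.

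Pathway participants have more routes by which a referral could come to light. They have outcome data collected at 12 months, a history form that asks about previous hepatology review, and requested consent to health care usage data from Services Australia. None of these is stated for the controls.

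If capture is lower in the control period, both limbs of H3 are distorted, in opposite directions. A rise in high-risk referral could appear without any real change, and a real fall in low-risk referral could be hidden. The planned incremental cost per appropriate referral depends on referral counts. If it uses these counts, and an appropriate referral means a high-risk one, the incremental number of referrals would be overstated.

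**Working it through.** **1. The plan's own figure.** The only design calculation is a 95% confidence interval of 15.4 to 25.5%. Inputs (Sample size and statistical power): 400 × 0.60 = 240 with NAFLD, and 240 × 0.20 = 48 with advanced fibrosis. The Wilson interval for 48/240 is 15.43 to 25.52%, which reproduces it. It says nothing about referral, so the plan gives no referral rate, capture fraction or control-group size. Everything below is assumed.

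**2. Model.** Let r be the true proportion referred, the same in both periods (no effect), s the share of usual-care referrals visible in the site record, and pathway capture complete.

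- Observed usual-care rate: r × s
- Spurious difference: r × (1 − s)
- Spurious risk ratio: 1/s
- Chance that a two-sided 5% test rejects, with n per period, d = r − rs and p̄ = (r + rs)/2: Φ[(d − 1.96·SE0)/SE1] + Φ[(−d − 1.96·SE0)/SE1], where SE0 = √[2p̄(1 − p̄)/n] and SE1 = √{[r(1 − r) + rs(1 − rs)]/n}

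**3. All patients, r = 8%, n = 400 per period.** Worked for s = 0.7: rs = 0.056, d = 0.024, p̄ = 0.068, SE0 = 0.0178, SE1 = 0.0178. The first term is Φ(−0.61) = 0.27 and the second is negligible.

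| Site capture s | Observed usual care | Spurious risk ratio | False rejection |
|---|---|---|---|
| 90% | 7.2% | 1.11 | 7% |
| 70% | 5.6% | 1.43 | 27% |
| 50% | 4.0% | 2.00 | 66% |

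The result depends on the rate. For the same three values of s, false rejection is 6%, 13% and 30% at r = 3%, and 8%, 33% and 77% at r = 10%.

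**4. High-risk patients only.** Take 48 per period. This is the plan's advanced-fibrosis number used as a stand-in, with the control number assumed equal. At r = 50%, the spurious gain is 5, 15 or 25 points, and false rejection is 8%, 32% or 72%. At r = 8% and s = 50% it is only about 13%.

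**5. Low-risk limb.** Assume true referral falls from 20% to 10%. The observed fall is 0.20 × s − 0.10, which is 8, 4 or 0 points instead of 10. The same error now works against the pathway.

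**6. Equal capture in both periods.** The no-effect difference stays at 0, because rs − rs = 0. A true low-risk fall of 10 points shrinks to 10 × s, which is 9, 7 or 5 points. A false effect therefore needs capture to differ between periods.

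**The case against.** A reader might infer that usual-care referrals are definitely under-counted and that Aim 3 is therefore biased in favour of the pathway. The documents do not support that.

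- **Referrer.** The GP is named as the person arranging referral only for the pathway. Nothing says who referred under usual care. The Beacon team includes GPs with a special interest and an endocrinologist, who could have referred themselves, and a GP's referral could be copied to the clinic. This stands: the statement is that referrals may be missed.
- **Differential capture.** No source is named for pathway referrals. If site records were used there too, the same blind spot would apply. Sending a letter that advises referral is the intervention, not a means of counting referrals. This also stands. Fuller pathway capture is plausible from the prospective follow-up and consented data, but it is not documented.
- **Direction.** Missed control referrals hurt the pathway on the low-risk limb, so a general claim that the comparison favours the pathway is wrong.
- **Size.** The percentages follow from the assumed rate, capture and group size, as steps 3 and 4 show.
- **Costs.** The equal-availability promise in Resource use and costs may cover referral counts, since its list need not be exhaustive. It weakens any flat statement that the cost result is biased. It is not tied to the Aim 3 outcome.
- **Condensed article.** Data-source detail is often left to a full protocol. That does not dispose of the point, because the article states the control source positively and that source fits the outcome poorly.

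**Conclusion.** The point holds as a risk of differential ascertainment. The control count of Hepatology referrals rests on retrospective site records that can miss referrals made by an outside GP. Pathway participants have prospective and consented sources that controls are not stated to have. If capture is lower under usual care, a rise in overall or high-risk referral is inflated and a fall in low-risk referral is masked.

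The size cannot be derived from the documents. Capture of 90% does little harm: false rejection is about 7% against a nominal 5% in the 8% example. Capture of 50 to 70% could be serious, at 66% to 27% under the same assumptions (400 per period, complete pathway capture, no true effect). This concerns a secondary aim and can be corrected before the audit is analysed, so the change should be made.

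**What to change.** For Aim 3, and for the referral counts used in the cost per appropriate referral:

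1. Ascertain referral in both cohorts from one receiving-end source, the Metro South Hepatology referral or appointment records, over windows of equal length.
2. Use case-note audit only as a supplement, applied identically to both cohorts.
3. State the expected direction of any residual bias separately for high-risk and low-risk referral.

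This extends to Aim 3 the equal-availability principle that the article already adopts for costs.

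The cost is a short change to the outcome definition and a data request. The consent waiver for controls must be worded to cover these records, since it is described only for patient medical records. The article does not say that Hepatology referral records are among the administrative collections it plans to use, so access has to be confirmed. Private or out-of-district referrals would still be missed, but in both periods, with no evident reason for the loss to differ between them.

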
### Statistical analysis

#### Sample size and statistical power

We aim to recruit at least 400 patients with T2D, anticipating ~ 60% to have NAFLD (*n* = 240). If 20% of these have advanced fibrosis [8] then the 95% confidence interval will be 15.4 to 25.5%. This will provide sufficient confidence that the observed rate using the pathway differs substantially from historical detection rates of < 5% [39].

#### Data analysis

Differences in the proportion of patients diagnosed with NAFLD (Aim 1), identified to have advanced fibrosis/cirrhosis (Aim 2), referred to Hepatology (Aim 3), and enrolled in a surveillance program for HCC (Aim 4) before and after implementation of the intervention will be assessed using statistical tests for categorical data (e.g. Pearson’s chi-squared test, McNemar test). Where appropriate we will use regression models to identify associations between variables (eg the association between treatment group (pathway vs. usual care) and clinical and sociodemographic factors).

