## Methods/design

### Overview

The non-alcoholic fatty liver disease: implementing the right care in the right place at the right time (NAFLD-RRR) study is a quasi-experimental study with a prospective intervention and historical control group. The intervention aims to incorporate a community care pathway for liver fibrosis screening into routine care for T2D. The study protocol (Version 6, 9th Feb 2022) includes in-depth phenotyping of participants including demographic details, metabolic co-morbidities, anthropometric measurements, alcohol consumption, smoking status, current medications and average daily physical activity. During a single assessment, liver steatosis and stiffness are measured using an EchoSens FibroScan Mini+ 430. The patient record is interrogated for the most recent haematological and biochemical parameters, lipid profile, and abdominal radiology. Patients are also asked for consent to collect health care usage data from a national Government agency, Services Australia. These data will be used to determine longitudinal health outcomes and facilitate an accurate and thorough analysis of health care usage and economic costs.

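### The same three clinics supply both cohorts, but the tests named for the before-after comparison ignore clinic, so a change in clinic mix between periods could enter the estimated pathway effect

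*Protocol article*

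**What the plan says.** The Overview describes a "quasi-experimental study with a prospective intervention and historical control group". Design and setting states that "The study will be conducted in 3 “Beacon” diabetes clinics". Under Secondary outcomes, the control cohort is defined thus: "Usual care data will be collected retrospectively from the three study sites for the year prior to recruitment commencement". The data therefore form three before-after pairs, one per clinic.

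Data analysis covers Aims 1 to 4 in one sentence. Differences in proportions "before and after implementation of the intervention will be assessed using statistical tests for categorical data". Two tests are named there as examples: "assessed using statistical tests for categorical data (e.g. Pearson’s chi-squared test, McNemar test"). It then adds: "Where appropriate we will use regression models to identify associations between variables". The example given there is "the association between treatment group (pathway vs. usual care) and clinical and sociodemographic factors". The article nowhere names clinic as a stratum, covariate or cluster.

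**The concern.** Pearson's chi-squared treats each period as one pooled sample. McNemar pairs individual patients and does not use clinic either. A pooled proportion is a weighted average of the clinic proportions, with weights equal to each clinic's share of that period's patients. If the shares change, the pooled proportion can move although nothing changed inside any clinic.

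A change in shares is plausible. Controls come from a records audit under a consent waiver (Secondary outcomes). Pathway participants are those reached by text and telephone before an appointment who agree to take part (Participant recruitment). These processes need not yield the same clinic shares. The control outcomes are recorded diagnoses and referrals, and these depend partly on local habit.

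At stake are the size of the reported pathway effect and, in less favourable cases, the error rate of the test.

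**Working it through.** **1. The plan's own figure.** Sample size and statistical power gives 20% of 240, that is 48/240, and says "then the 95% confidence interval will be 15.4 to 25.5"%. The Wilson interval is (p + z²/2n ± z√(p(1−p)/n + z²/4n²)) / (1 + z²/n). With p = 0.20, n = 240 and z = 1.96 it gives 15.43 to 25.52%. The figure reproduces.

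**2. Bias from a change in mix.** With no change inside any clinic, the spurious difference is the sum over clinics of (change in share × clinic rate). Assume equal thirds before, with 10 or 20 points of share moved from the lowest-rate to the highest-rate clinic:

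- Rates 2/5/8%: 0.10 × 6 = 0.6 points; 0.20 × 6 = 1.2 points.
- Rates 10/20/30%: 0.10 × 20 = 2 points; 0.20 × 20 = 4 points.
- Rates 10/30/50%: 0.10 × 40 = 4 points; 0.20 × 40 = 8 points.

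**3. Error rate when clinic rates vary at random.** Assumptions: three clinics, n patients per period, mean rate p, clinic variance ICC × p(1−p), clinic effects stable over time, no pathway effect. Move a share δ from one clinic to another.

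- Variance of the spurious difference: δ² × 2 × ICC × p(1−p).
- Sampling variance assumed by the pooled test: 2p(1−p)/n.
- Ratio of the two: nδ²ICC.
- Allowing for the smaller variance within clinics, rejection ≈ P(|Z| > 1.96/√(1 − ICC + nδ²ICC)).

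For n = 400:

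| Mix | ICC | 1 − ICC + nδ²ICC | Rejection at nominal 5% |
|---|---|---|---|
| Unchanged | 0.01 | 0.99 | 4.9% |
| Unchanged | 0.05 | 0.95 | 4.4% |
| 10-point shift | 0.01 | 0.99 + 0.04 = 1.03 | 5.4% |
| 10-point shift | 0.05 | 0.95 + 0.20 = 1.15 | 6.8% |
| 50/33/17 to 17/33/50% | 0.01 | 0.99 + 0.44 = 1.43 | 10.1% |
| 50/33/17 to 17/33/50% | 0.05 | 0.95 + 2.18 = 3.13 | 26.8% |

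Simulation with beta-distributed clinic rates and means of 5 to 20% agrees: about 5 to 7% for the 10-point shift, 9.5 to 10% for the reversal at ICC 0.01, and 23 to 27% at ICC 0.05. A Cochran-Mantel-Haenszel (CMH) test stratified by clinic rejects about 5% throughout.

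**4. A harsher case.** If the mix moves exactly along a fixed gradient of clinic rates, pooled chi-squared rejects as follows for 10- and 20-point shifts (20,000 simulated trials, 400 per period):

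- Rates 2/5/8%: 6.2% and 11.0%.
- Rates 10/20/30%: 10.8% and 27.5%.
- Rates 10/30/50%: 23.2% and 66.8%.

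CMH stays at 4.8 to 5.2%. With the mix unchanged, pooled chi-squared gives 4.8 to 5.0%.

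**5. Against the planned contrasts.** Advanced fibrosis in 48 of 400 is 12% of all participants, against a historical rate below 5%. With clinic rates of 0/5/10%, placing every patient in the highest-rate clinic raises the pooled rate only from 5% to 10%. With usual-care NAFLD rates of 10/30/50%, the maximum is 50%, short of the anticipated 60%.

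**6. Smaller denominators.** High-risk referral and HCC surveillance are counted within subgroups. With an assumed 48 patients per period, a full reversal at ICC 0.05 adds 48 × 0.33² × 0.05 = 0.26 to 0.95, and rejection is about 7.5%. At ICC 0.01 it is about 5.5%. Simulation gives roughly 5 to 8%. Low-risk referral has a larger denominator. With an assumed 240 − 48 = 192 per period, the same reversal adds 192 × 0.33² × 0.05 = 1.05, and rejection is about 17%.

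**The case against.** The strongest reply is that this is a journal article. The full protocol and analysis plan are not shown, and the choice of strata is often left to them. The two tests are only examples, and regression is left open, so a clinic-stratified analysis would not contradict the text. This stands as a limit on severity: nothing is stated falsely. It does not dispose of the point, because both tests the article chose to name ignore a design factor of the study, and its regression example lists other factors.

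The mix shift is also undocumented. Recruitment is sequential, everyone attending is to be offered participation, and controls meet the same criteria apart from consent. Differing consent alters the mix only if uptake differs between clinics, and the article does not say that it does. This stands, so the finding is conditional.

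The upper end of the 9 to 27% range needs a complete reversal of clinic shares at ICC 0.05, which is extreme. That too stands.

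Two stronger readings are tempting and are not supported:

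- A reader might infer that pooling is wrong in itself. It is not: with an unchanged mix and stable clinic effects, the pooled test keeps its level.
- A reader might infer that the sample-size interval should be widened by a design effect. It reproduces as stated. A wider one would need an invented ICC and would treat three fixed study sites as a sample of clinics. On the figures examined (11.1 to 33.3% at ICC 0.05), it would still exclude 5%.

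**Conclusion.** The point holds in a limited, conditional form. The same clinics feed both cohorts, the named tests do not use clinic, and a clinic-mix effect would enter the before-after difference if two things are true together: clinics differ in their rates, and their shares differ between periods. The article shows neither.

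Under the random-clinic assumptions, the error rate is barely affected by a 10-point shift and clearly affected only by a large one. It is worse if the shift follows a steep gradient in clinic rates. These results rest on an assumed 400 patients per period, an assumed ICC or set of clinic rates, and clinic effects that are stable over time.

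A reader might infer that the primary conclusions are in doubt. The calculations do not support that: under the assumed clinic rates, even an extreme change in mix falls short of the planned rates. The main consequence is a distorted effect size. Inflation is small for outcomes counted in a few dozen patients and larger for low-risk referral.

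**What to change.** In Data analysis, make the before-after comparison for Aims 1 to 4 clinic-stratified. Either of these would serve:

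- a CMH test with a stratified risk difference; or
- logistic regression of the outcome on period, with clinic as a fixed effect.

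Allow an exact or simple pooled test where strata are too sparse, as is likely for HCC surveillance. Report the clinic mix in each period and each clinic's own before-after difference. Leave the interval under Sample size and statistical power unchanged.

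The cost is a wording change and one extra table. Usual-care data are collected by site, so clinic should be known for every patient, and no new patients are needed.

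One limit should be stated in the plan. Stratification does not remove variation in clinic effects between periods. With ICC 0.05 and a correlation of 0.8 between a clinic's effects in the two periods, the stratified test still rejected a true null in 19 to 21% of simulated trials. Three clinics cannot estimate that variation reliably, which is why the clinic-level differences should be shown.

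### For Aims 1 to 4 the article states only unadjusted tests for a non-randomised comparison with historical controls, and one named test needs pairs it does not define

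*Protocol article*

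**What the plan says.** The Overview calls the trial a "quasi-experimental study with a prospective intervention and historical control group". Under Design and setting, "Study outcomes will be compared to a cohort who received “usual care” at the community diabetes clinics in the 12-months prior to implementation" of the pathway. Under Secondary outcomes, the article adds that "Eligibility and exclusion criteria of controls will be the same as the intervention group except for patient consent", because a waiver will be sought for the record audit.

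The Data analysis section takes Aims 1 to 4 together: NAFLD diagnosis, advanced fibrosis or cirrhosis, hepatology referral and HCC surveillance. Before-and-after differences in these proportions "will be assessed using statistical tests for categorical data (e.g. Pearson’s chi-squared test, McNemar test". It continues: "Where appropriate we will use regression models to identify associations between variables". The single example is "the association between treatment group (pathway vs. usual care) and clinical and sociodemographic factors".

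The article states no adjusted, matched, weighted or stratified estimate of the pathway effect. Confounding is mentioned only in the Discussion, for the longitudinal health outcomes. Yet the audit of controls is to collect "demographic information, anthropometric measurements (height, weight, BMI, waist circumference), relevant metabolic co-morbidities, diabetes medications", and the Overview and Table 1 provide for the counterparts in pathway patients.

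**The concern.** In a historical-control design the crude difference between cohorts mixes the pathway effect with any difference in who was seen and who agreed to take part. Consented volunteers from one period are set against an audit cohort from another that needed no consent. If they differ in BMI, comorbidity or clinic, and these influence whether liver disease is recorded, referred or followed up, a chi-squared test counts that difference as a pathway effect.

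Regressing group on patient characteristics would show such imbalance but would leave the outcome comparison unchanged. The per-protocol sensitivity analysis could add to the imbalance. It keeps only patients who could be scanned, and the article puts invalid stiffness measurements, caused by body habitus or skin-to-capsule depth, at 9–15% of examinations. Controls face no such exclusion.

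McNemar's test compares two measurements on the same or matched units. The article describes two cohorts and no matching.

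**Working it through.** **1. The plan's own figure.** The sample size section expects 60% of 400 = 240 patients with NAFLD, 20% of whom (48) have advanced fibrosis, with a 95% CI of 15.4 to 25.5%. The Wilson interval for 48/240 reproduces it:

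- centre = (0.2 + 3.8416/480) / (1 + 3.8416/240) = 0.2080/1.0160 = 0.2047
- half-width = 1.96 × √(0.2 × 0.8/240 + 3.8416/(4 × 240²)) / 1.0160 = 0.0504
- interval = 15.43% to 25.52%

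The figure is correct. It is a one-sample precision statement and does not bear on confounding between two cohorts.

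**2. Bias in a crude test when the pathway does nothing.** The article gives no covariate distributions by group, so these inputs are assumptions: 400 per group, a 10% outcome rate in controls, and one binary confounder with risk ratio r for the outcome and prevalence a (pathway) or c (controls).

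Expected pathway rate = 0.10 × [1 + a(r − 1)] / [1 + c(r − 1)].

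| a vs c | r | Pathway rate | Crude risk ratio | Chi-squared false-positive rate |
|---|---|---|---|---|
| 60% vs 50% | 2 | 0.10 × 1.6/1.5 = 10.7% | 1.07 | 6% |
| 60% vs 40% | 2 | 0.10 × 1.6/1.4 = 11.4% | 1.14 | 10% |
| 70% vs 40% | 3 | 0.10 × 2.4/1.8 = 13.3% | 1.33 | 31% |

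The last column is Φ[(d − 1.96·s₀)/s₁] + Φ[(−d − 1.96·s₀)/s₁]. Here d is the rate difference, s₀ its pooled and s₁ its unpooled standard error. For the last row d = 0.0333, s₀ = √(2 × 0.1167 × 0.8833/400) = 0.0227 and s₁ = √((0.1333 × 0.8667 + 0.10 × 0.90)/400) = 0.0227. The first term is Φ(−0.49) = 0.31 and the second is negligible.

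A concrete version, also assumed: recording or referral in 15% of obese and 5% of non-obese patients, with obesity in 70% of one cohort and 55% of the other. The rates are 0.70 × 0.15 + 0.30 × 0.05 = 12.0% and 0.55 × 0.15 + 0.45 × 0.05 = 10.5%. That is a 1.5-point difference with no pathway effect.

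**3. Could confounding explain the expected detection contrast?** The article sets its 20% against historical detection below 5%. The E-value, RR + √[RR(RR − 1)], is the risk ratio that a confounder would need with both group and outcome to explain the contrast fully.

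- 20% vs 5%: RR = 4.0; 4.0 + √(4.0 × 3.0) = 7.5
- Whole cohort, 48/400 = 12% vs 5%: RR = 2.4; 2.4 + √(2.4 × 1.4) = 4.2

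Taking the historical rate at its 5% ceiling makes both values minima. The 12% assumes a valid scan in every recruit.

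**4. McNemar.** Between the cohorts the article defines no pairs. Within pathway participants a pair does exist: Table 1 records previous NAFLD diagnosis, and the scan gives the pathway diagnosis.

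**The case against.** The best reply is that the article only gives examples. Both the tests and the regression are introduced as such, regression is allowed where appropriate, and the example does not say which variable is the dependent one. A reader might infer that measured confounding will remain in every effect estimate. The text does not support that: an outcome model with group and covariates is not excluded, costs are modelled separately, and a covariate list may properly sit in an analysis plan not shown here. What remains is that the methods the article does name for Aims 1 to 4 are crude, and that no stated use of regression yields an adjusted pathway effect.

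A reader might also infer that the cohorts overlap, so that the chi-squared independence assumption fails. Overlap is plausible, since the clinics are the same, but it is not documented. Positive within-person correlation would reduce the variance of the difference and make the ordinary test conservative.

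Nor does scan acceptance define the main comparison. The main analysis is intention-to-treat by recruitment, and only the sensitivity analysis is limited to scanned patients. Consent selection still applies to both.

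McNemar is listed as one example and is not expressly assigned to the cohort comparison. It has a legitimate within-participant use. The fair criticism is that the article does not say what is paired.

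Finally, a model with many covariates may not be estimable for Aim 4, because cirrhosis is a subset of about 48 expected cases of advanced fibrosis. That stands and shapes the remedy.

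**Conclusion.** The point holds in limited form. The stated comparison for Aims 1 to 4 is unadjusted in a design where the groups differ in calendar period and in consent, and the one regression example does not, on its natural reading, repair this. The paired test has no defined pairs between the cohorts.

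The consequence is moderate. For Aims 1 and 2 the reported size of effect may be biased, but the finding of increased detection is unlikely to be overturned if the expected contrast appears. For Aims 3 and 4 the article projects no contrast, so a bias like those in the table could change the conclusion. The false-positive rates of 6–31% rest wholly on assumed prevalences, risk ratios, group sizes and a 10% control rate. They show how the bias arises and are not an estimate for this trial. This should be fixed; it does not invalidate the study.

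**What to change.** - **Aims 1 to 3:** make the main estimate a regression of the outcome on group, or standardisation or propensity weighting. Adjust for a short prespecified set of covariates collected in both groups: age, sex, BMI, metabolic comorbidity, diabetes medication and clinic. Report an adjusted risk difference with 95% CI.
- **Aim 4, and wherever events are sparse:** use a reduced or penalised model, or report the crude result as descriptive.
- **Chi-squared:** keep it as the crude supportive result.
- **McNemar:** restrict it to within-participant comparisons, such as previously recorded NAFLD against the pathway diagnosis.
- **Overlap:** if the audit finds patients in both periods, use cluster-robust standard errors on the patient identifier.

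The cost is a change of wording and a little more analysis. No new variables are needed, but control covariates come from whatever the records hold, so missing values, BMI for example, will have to be handled and may limit the adjustment.
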